### Analyses

#### Feasibility

The decision as to whether to progress the study to a future large-scale RCT will be based on a number of criteria. These include the number of patients we are able to recruit, the proportion of patients retained in the study, the proportion of patients completing the real rTMS/sham intervention, the acceptability of real rTMS/sham intervention and the effect sizes of treatment outcomes. At the end of the study, these factors will be used by the study team to decide the case for progressing to a substantive RCT.

#### Clinical outcomes

Analyses will use the intention-to-treat principle. To determine quality, completeness and variability of the outcome measures, descriptive statistical analyses and graphical methods will be used. The size of the treatment effect on each outcome measure (BMI, questionnaires, neuropsychological processes) will be the difference in outcome data between those in the two treatment conditions at post-treatment and follow-up. Group differences will be estimated using linear mixed effects regression models, controlling for the baseline level of the outcome. The aim of the analysis is to establish a suitably precise effect size for the primary outcome in a future large-scale RCT at the post-treatment assessment. Additionally, multiple regression models will permit exploration of the relationship between changes in the varying neuroimaging measures and symptom improvement on questionnaire and task-based outcomes.

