#### Inclusion criteria

Male or female participants will be included if they are right-handed, have a current DSM-5 diagnosis of AN, are aged 18 or over and meet the following criteria for SEED-AN: (1) an illness duration of 3 years or more (this is the minimum illness duration cited in the literature after which treatment outcomes tend to be poorer [11, 25]); (2) a BMI between 14 and 18.5 kg/m^2^ (the upper BMI cut-off of 18.5 kg/m^2^ was chosen pragmatically for comparability with other studies, for example, [23] and the lower BMI limit of 14 kg/m^2^ was selected as a safety precaution); and (3) at least one previous adequate course of ED treatment (for example, one 6-month course of specialist outpatient psychotherapy, specialist day care or in-patient treatment for refeeding). All participants must have agreement from their ED clinician or their GP to take part.

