#### Sample size

As this is a feasibility study, no a priori sample calculation has been conducted. This study aims to provide effect sizes on which future large-scale studies can be powered. Total sample sizes of *N* = 24–50 have been recommended for feasibility trials with outcomes measured on a continuous scale, mainly because estimates of the standard deviation for normally distributed variables tend to stabilise around this size [65, 66]. We have chosen a sample size of *N* = 40 (that is, at the upper end recommended for feasibility trials). Assuming the attrition to follow-up rate is a = 0.10 (as found in our previous AN trials [15, 67], [name] et al., unpublished observations and applying an attrition correction factor of 1/(1-a), we will need a total sample size of *N* = 44 (22 participants per group).

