### Randomisation

Generation and implementation of the randomisation sequence will be conducted independently from the trial team by the King’s Clinical Trials Unit (CTU). Once the baseline assessment has been carried out and the patient is recruited and has consented to the trial, the researcher will enter patient ID and stratification details into the web-based CTU system. Patients will then be allocated to one of the two trial arms using a restricted stratified randomisation algorithm, stratifying by prognostic factors (type of AN - binge-purge or restricting; intensity of TAU - low (outpatient) or high (daypatient)). The stratification will be implemented by minimised randomisation with a random component. The first n cases (n will not be disclosed) will be allocated entirely at random to further enhance allocation concealment.

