### Intervention

#### Commonalities between both groups

In both groups participants will receive 20 real or sham rTMS sessions over 20 consecutive weekdays. Testing/experimental sessions will last between 40–60 minutes, including preparation time, 20 minutes of rTMS and questionnaire administration. Throughout the study, participants will be able to access or continue TAU as recommended by their treating team. TAU will range from GP care only to specialist eating disorder care (day-care or outpatient only).

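### Allocation is minimised on AN type and TAU intensity, but the stated effect model names only the baseline outcome; precision is lost to the extent that those factors predict outcome beyond baseline

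*Protocol article*

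**What the plan says.** **Allocation.** The Randomisation section of the protocol article describes "stratifying by prognostic factors (type of AN - binge-purge or restricting; intensity of TAU - low (outpatient) or high (daypatient"). On method it adds: "The stratification will be implemented by minimised randomisation with a random component". There is also a run-in of simple randomisation: "The first n cases (n will not be disclosed) will be allocated entirely at random". Neither the size of the random component nor the length of the run-in is given.

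**Effect model.** Under Analyses, Clinical outcomes: "Group differences will be estimated using linear mixed effects regression models, controlling for the baseline level of the outcome". The same paragraph gives the purpose: "The aim of the analysis is to establish a suitably precise effect size for the primary outcome in a future large-scale RCT". The shown text nowhere brings AN type or TAU intensity into a model.

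**TAU range.** Under Intervention, Commonalities between both groups: "TAU will range from GP care only to specialist eating disorder care (day-care or outpatient only"). The Inclusion criteria are consistent with GP-managed entry: "All participants must have agreement from their ED clinician or their GP to take part".

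**The concern.** Minimising on a prognostic factor makes the arms alike on it, so the factor contributes little to the real sampling variation of the treatment difference. If the model omits the factor, its contribution to the outcome stays in the residual variance. The model-based standard error then reflects variation that the allocation has largely removed. Intervals come out too wide and the test rejects less often than its nominal level. The estimate itself stays unbiased.

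This trial's main quantitative product is a set of effect estimates. The Analyses section wants them suitably precise, and the Feasibility section lists effect sizes among the criteria for progressing to a larger trial. Precision that the design has already secured should not be lost in the model.

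A smaller matter sits beside this. The TAU factor must be entered before allocation, and its two levels as labelled do not mention patients whose usual care is GP care only.

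**Working it through.** **1. The plan's own figure.** The Sample size section targets 40 and inflates for dropout: "Assuming the attrition to follow-up rate is a = 0.10". 40/(1 - 0.10) = 44.4, stated as 44; conversely 44 x 0.9 = 39.6. The figure reproduces, and 40 analysed is the right basis for what follows.

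**2. Assumptions, because the documents give no values.** Baseline-outcome correlation 0.5 within factor levels; factor prevalences 0.5 and 0.3; each factor shifts the score by 0.5 or 0.8 SD; minimisation favours the balancing arm with probability 0.8 after 8 simple-random allocations; a linear model at a single time point stands in for the mixed model.

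**3. Closed form, factors act on the outcome only.** Let v be the outcome variance due to the factors.
- 0.5 SD: v = 0.25 x (0.5 x 0.5 + 0.3 x 0.7) = 0.25 x 0.46 = 0.115.
- 0.8 SD: v = 0.64 x 0.46 = 0.294.
- Residual variance with baseline and factors in the model: 1 - 0.5² = 0.75. With baseline only: 0.75 + v.
- SE ratio, baseline-only to adjusted: sqrt(0.865/0.75) = 1.07 and sqrt(1.044/0.75) = 1.18.

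**4. Closed form, factors shift baseline and outcome equally.** Baseline now carries much of the factor information. The residual variance given baseline only is (1 + v) - (0.5 + v)²/(1 + v).
- 0.5 SD: 1.115 - 0.615²/1.115 = 0.776; ratio sqrt(0.776/0.75) = 1.02.
- 0.8 SD: 1.294 - 0.794²/1.294 = 0.807; ratio sqrt(0.807/0.75) = 1.04.

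The two degrees of freedom spent on the factors take just under 1% off these ratios in practice.

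**5. Simulated trials (3,000 to 4,000 per case, minimised as in step 2).**

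| Factors act on | Shift | SE, baseline only | SE, adjusted | Ratio | Type I error, baseline only |
|---|---|---|---|---|---|
| Outcome only | 0.5 SD | 0.297 | 0.277 | 1.07 | 3.5-3.6% |
| Outcome only | 0.8 SD | 0.327 | 0.277 | 1.18 | 2.5-2.7% |
| Baseline and outcome | 0.5 SD | 0.280-0.281 | 0.278 | 1.01 | 4.3-4.8% |
| Baseline and outcome | 0.8 SD | 0.286-0.287 | 0.278-0.279 | 1.03 | 4.3-4.8% |

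In the outcome-only rows, the baseline-only SE can also be set against the actual sampling SD of its own estimate: 0.297/0.278 = 1.07 and 0.327/0.289 = 1.13. In the shared rows, the SE agrees with the sampling SD (0.280 against 0.279; 0.286 against 0.287). What remains there is a small loss of precision against the adjusted model, without visible miscalibration.

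**6. By share of variance.** If the factors explain a share R² of the outcome variance left after baseline, the large-sample SE ratio is 1/sqrt(1 - R²). A separate set of 4,000 simulated trials per case, 44 minimised and 40 analysed, gave:

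| R² | Closed form | Simulated ratio | Type I error, baseline only |
|---|---|---|---|
| 0 | 1.00 | 0.99 | about 5% |
| 0.05 | 1.03 | 1.02 | 4-5% |
| 0.10 | 1.05 | 1.05 | 4-4.5% |
| 0.20 | 1.12 | 1.11 | about 3% |
| 0.30 | 1.20 | 1.19 | 2.5-3% |

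The adjusted model stayed at about 4.6-5.7% throughout. At R² = 0 its SE was 0.321 against 0.319, a cost of 0.6%.

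**7. TAU levels side by side.** Randomisation has two levels, low (outpatient) and high (daypatient). Intervention has three kinds of usual care: GP only, outpatient, day care. The shown text does not say under which level the first is entered.

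**The case against.** **The analysis plan is not shown and may add the factors.** The model sentence is short, sits in a condensed article, and does not say that baseline is the sole covariate. That stands as a limit: a reader might infer that the protocol excludes the allocation factors, and it does not. But the sentence does name the covariate to control for. A better model than the one stated is available at almost no cost, so the point is more than a missing detail.

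**Baseline adjustment may already do most of the work.** Many outcomes are repeated scores on one scale (BMI, EDE-Q, DASS-21). A factor that separates patients after treatment may well separate them before it. This stands, and it is why the low end of the range is 1-3%. A reader might infer that the standard errors are simply too wide; the documents do not support that without a condition, because they label the factors prognostic but give no strength.

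**Consequences can be overdrawn.** The trial names no primary outcome and makes no power calculation, so a loss of power is not a failure against any stated design target. A reader might also infer that an inflated residual SD will feed the next sample size calculation. The Aims promise effect sizes and standard deviations of outcome measures, and do not say which SD will be used.

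**The GP-only gap is one of labelling.** GP care alone is less intensive than specialist outpatient care, so low intensity is the natural reading, and the entry rules may be in the trials unit's documents. A reader might infer that such patients cannot be randomised or that balance is compromised; nothing shown supports this.

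**Conclusion.** The point holds in conditional form. The stated model leaves out the two factors on which allocation is balanced. If they predict outcome beyond baseline, the reported uncertainty is larger than it need be and the test errs on the conservative side. There is no bias in the effect estimate.

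Under the assumptions listed, the standard error is about 1-3% wider than the adjusted one when the factors act equally on baseline and outcome, and about 7-18% wider when they act on the outcome only. If they are not prognostic there is no loss. Which case applies cannot be settled from the documents, and it may differ between outcomes. This is an inexpensive improvement to the analysis and does not threaten validity. The TAU labelling gap is real but minor, with no demonstrated consequence.

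**What to change.** In Analyses, Clinical outcomes, add AN type and TAU intensity to the effect model as fixed effects beside the baseline value, using the values entered at randomisation. Both are already collected. The cost is one line of text and two degrees of freedom: at a single time point with 40 analysed, 40 - 3 = 37 becomes 35. If the factors explain nothing, the standard error rises by under 1%.

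In the Randomisation section, reconcile the two TAU levels with the range of usual care given under Intervention. State the level under which patients with GP care only are entered in the randomisation system, and carry the same coding into the model. This concerns data entry only and changes nobody's care.

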### Aims

The specific objectives of the proposed feasibility study are to:establish the feasibility of conducting a large-scale RCT of rTMS in patients with SEED-AN by assessing recruitment, attendance and retention rates;determine the best instruments for measuring outcomes in a full trial by examining the quality, completeness and variability in the data;estimate the treatment effect sizes and standard deviations for outcome measures to inform the sample size calculation for a large-scale RCT;evaluate whether the treatment is operating as designed by analysing process measures, for example, within-session visual analogue scales (VAS) of key ED symptoms;explore patients’ views on the acceptability, credibility, tolerability and experience of rTMS;obtain information about patients’ willingness to undergo random allocation to 20 sessions of real or sham rTMS;investigate neurocognitive changes underlying treatment response; andinvestigate neural mechanisms underlying treatment response, including changes in structure, cerebral blood flow and in regional activity and functional connectivity at rest and during computer-based tasks assessing behavioural control.

Tentative underpinning hypotheses are based on pilot studies previously conducted by our group and others in patients with EDs [53, 55, 58, [name] et al., unpublished observations] and other disorders that are frequently comorbid with EDs, including depression [60–62] and addictions [63]. It is predicted that, compared to sham rTMS treatment, 20 sessions of high-frequency rTMS applied to the left DLPFC will:reduce AN symptomatology, encourage an increase in weight/BMI and improve related psychopathology (such as depression, anxiety and stress) and quality of life;improve self-regulatory control, emotion regulation, attentional-bias processes, and food choice behaviour. Improvements in self-regulatory control abilities will be associated with changes in task-based neural activity and connectivity between the DLPFC and the inhibitory control network (the right inferior frontal gyrus, pre-supplementary motor area) and areas implicated in reward processing (for example, the ventral striatum [64]);alter neural activity in the DLPFC at rest (for example, cerebral blood flow) and during task performance during functional magnetic resonance imaging (fMRI), which will be correlated with symptom improvement; andbe considered by patients as an acceptable and useful treatment adjunct for AN.

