Although we are using the most up-to-date equipment with an improved sham coil that elicits a more realistic TMS-like sensation, it is not clear whether participants, especially those who may have previous experience of rTMS in other research studies, will be able to distinguish between the real and sham treatment and what impact this will have on attrition rates. However, in our previous RCT of a single rTMS session in people with AN there was no difference between groups in the ability to correctly guess stimulation type [[name] et al., unpublished observations].

It will be important to ascertain patients’ willingness to undergo random allocation to real or sham rTMS. This is not trivial, as rTMS is a relatively demanding treatment, requiring daily attendance for an extended period. However, this type of RCT is considered the gold-standard method of evaluating the clinical efficacy of rTMS treatment in other disorders, such as depression [50]. Providing participants who were randomised to receive sham rTMS with the opportunity to receive real rTMS after they have completed the study is thought to be critical in encouraging recruitment and participant retention. Addressing these challenges will be particularly useful in informing the development of future large-scale RCT of rTMS in EDs.

In summary, research into novel treatments for SEED-AN is essential. rTMS is a promising neuromodulatory technique that has shown preliminary benefit in AN, including individuals with SEED-AN. This innovative feasibility RCT will be the first to systematically assess the acceptability, efficacy and neural correlates of this promising treatment in comparison to an active control condition. This will provide a foundation for the development of future large-scale RCTs and, if the results are positive, will provide support for the implementation of this as a treatment adjunct in clinical practice.

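### The analysis aims for a suitably precise effect size and the plan would power later trials on it, but N = 40 rests only on stability of the SD and leaves the effect uncertain by about ±0.4 to 0.6 SD

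*Protocol article*

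**What the plan says.** The protocol article gives the effect estimates three tasks.

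- **Analyses, Clinical outcomes:** "The aim of the analysis is to establish a suitably precise effect size for the primary outcome in a future large-scale RCT". The time point named is the post-treatment assessment. Group differences come from linear mixed models that control for the baseline level of the outcome.
- **Sample size and Aims:** Sample size says the study is to supply effect sizes on which later large studies can be powered. The matching objective under Aims is softer: "estimate the treatment effect sizes and standard deviations for outcome measures to inform the sample size calculation for a large-scale RCT".
- **Analyses, Feasibility:** the criteria for progressing to a large trial are recruitment, retention, completion of the intervention, and finally "the acceptability of real rTMS/sham intervention and the effect sizes of treatment outcomes".

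On the number of patients, Sample size states: "As this is a feasibility study, no a priori sample calculation has been conducted". It cites a recommended range of 24 to 50 in total, mainly because the estimated SD of a normal variable stabilises there, and takes 40. With an attrition-to-follow-up rate of 0.10, this becomes 44, or 22 per group.

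**The concern.** The stated aim and the stated basis for the sample size concern different quantities. Enough patients to estimate an SD tolerably well are not enough to estimate a difference between two means well. No section connects the two, and the plan gives no target or expected width for the interval around the effect.

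The next trial is at stake. Required sample size varies with the inverse square of the target difference, so error in the observed effect is magnified when that effect is used for powering. A chance high estimate gives an underpowered trial. A chance low one gives a trial that looks infeasible.

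**Working it through.** **Inputs from the protocol article.** Target 40 evaluable (20 per arm); attrition 0.10; 44 randomised (22 per arm); adjustment for baseline.

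**Inputs assumed.** Correlation *r* between baseline and outcome, shown over a range; 90% power and two-sided 5% for the future trial; an observed difference of 0.4 SD as an example.

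**1. The plan's own figure.** 40 / (1 − 0.10) = 44.4, stated as 44. This reproduces within rounding (44 × 0.9 = 39.6) and is not disputed.

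**2. Precision of the effect.** In units of the outcome SD, with *n* per arm:

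half-width = t(0.975) × √[(2/n)(1 − r²)]

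Degrees of freedom are 2n − 2, less one when *r* > 0. Example for n = 20, r = 0.5: 2.026 × √(0.1 × 0.75) = 0.555.

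| r (assumed) | 20 per arm | 22 per arm |
|---|---|---|
| 0 | 0.640 | 0.608 |
| 0.5 | 0.555 | 0.527 |
| 0.7 | 0.458 | 0.435 |
| 0.8 | 0.384 | 0.365 |

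The 22-per-arm column applies if nobody is lost by post-treatment.

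**3. What an observed 0.4 SD would mean at r = 0.5.**
- 20 per arm: 0.4 ± 0.555 = −0.155 to 0.955.
- 22 per arm: 0.4 ± 0.527 = −0.127 to 0.927.

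**4. Consequence for powering.** n per arm = 2 × (1.96 + 1.2816)² / d² = 21.016 / d², without baseline adjustment, rounded up:
- d = 0.2: 526 per arm
- d = 0.4: 132 per arm
- d = 0.8: 33 per arm

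All three values of d lie inside both intervals in step 3. Compared with planning on 0.4, the required size is about four times larger at one and about four times smaller at the other. Baseline adjustment in the future trial would multiply all three sizes by the same factor, so the ratios stay.

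**5. Precision of the SD, the quantity on which N was justified.** With 38 degrees of freedom the 95% limits are √(38/χ²) at the two tails, or 0.817 to 1.289 times the estimate. Squared, that is a factor of about 0.67 to 1.66 on the future sample size. This uncertainty is material but bounded, whereas the interval for the effect in step 3 includes zero, where no finite sample size follows.

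**6. For scale.** A half-width of 0.3 SD (an illustrative target, not the protocol's) would need 2(1 − r²)(1.96/0.3)² = 86 per arm at r = 0, or 65 at r = 0.5.

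**The case against.** The strongest reply is that *suitably precise* has no number attached, so no numerical target is missed, and that a feasibility trial needs no power calculation. Both statements are true. The point is narrower: a property is claimed, the sample-size argument does not support it, and the interval that results is too wide for the use named under Sample size. A separate analysis plan could add confidence intervals, but it could not narrow them at this size.

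It can also be said that the widths are pessimistic, because the 10% loss is to follow-up while the precision aim is at post-treatment. Hence the 22-per-arm column, which changes little. A correlation of 0.8 would bring the half-width to 0.37 to 0.38 SD, still wide for powering.

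Some stronger readings are tempting and are not supported:

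- *Effect size decides go or no-go, so error rates for that decision can be computed.* It is the last of five criteria and has no threshold. Any error rate would depend on a cut-off that the reader invents.
- *The observed effect will be entered directly into the next sample-size calculation.* Aims says only that effect sizes and SDs will inform it. The sentence under Sample size is stronger, but does not say how the estimate would be used.
- *The trial is meant to justify clinical use.* The Discussion says: "if the results are positive, will provide support for the implementation of this as a treatment adjunct in clinical practice". This is conditional closing language. It is unclear whether it refers to this trial or to the future trials named in the same sentence, and it governs no analysis. Elsewhere the article calls its efficacy findings preliminary and its hypotheses tentative.

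**Conclusion.** The point holds as a mismatch between a stated aim and the design's justification. With 20 to 22 per arm, the 95% half-width is about 0.53 to 0.64 SD for correlations of 0 to 0.5, and 0.43 to 0.46 SD at 0.7. These figures rest on the usual normal-theory formula and on assumed correlations. Within that range an observed 0.4 SD leaves zero inside the interval, together with large effects, and the size of the future trial could be wrong by a factor of about four in either direction.

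The finding does not show that the trial is too small for feasibility, that N = 44 is wrong, or that the progression decision is faulty. The trial can still inform the next design, chiefly through the SDs and the feasibility rates. The correction is worth making but is not an obstacle to running the trial.

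**What to change.** - **Analyses, Clinical outcomes:** replace the promise of a suitably precise effect size with effect estimates and 95% confidence intervals, expected half-width about 0.4 to 0.6 SD, and name the assumed correlations.
- **Sample size and Aims:** say that this trial supplies the SD, with its uncertainty (95% limits about 0.82 to 1.29 times the estimate at 38 degrees of freedom), and that the future target difference will come from a justified important difference, not from the observed effect. How the uncertainty in the SD is allowed for can be left to the future trial's statistician.
- **Analyses, Feasibility:** let recruitment, retention, completion and acceptability drive progression, with effect estimates and their intervals as supportive information only. A formal rule that the interval must not exclude an important difference is not recommended. At 20 per arm and an assumed important difference of 0.4 SD, a treatment with no effect would pass about 78%, 71% and 60% of the time for r = 0, 0.5 and 0.7.

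**Cost:** wording only. No patient, visit or analysis model changes. The stated precision becomes less favourable, and the future trial may be planned larger.
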